### Blinding

In this investigation, all researchers involved in outcome assessments will be blinded to the group allocation of participants. During the intervention period, only unblinded researchers will be in contact with participants enrolled in the trial. In addition, all data analysis will be completed by personnel who are blinded to the intervention assignment. Participants will be unblinded after the 6 months and 7 days of assessment.

### Interventions

Theory-based educational measures delivered by a smart application

We developed the contents of the digital multimedia education intervention after reviewing the related literature and conducting several rounds of panel discussions. The panel members included a Cancer Epidemiologist, an Infectious Diseases Epidemiologist, a Senior Manager in a new media company and a researcher from one of the research centers of this project. We also formed a University advisory committee, which consisted of the project leader of each sub-center, authoritative experts in the field of cervical cancer prevention and treatment, and experienced experts in the field of epidemiology and health statistics. Additionally, we conducted a series of focus groups with 50 undergraduate girls and key information interviews with university counselors and health professionals. During such time we modified and refined the intervention content and finally determined that the best format to deliver the 7-day education intervention would be via smart devices such as a computer or mobile phone.

According to the IMB, mobile health intervention popularizes health-related knowledge, develops motivators to raise awareness of healthy behavior, and provides relevant behavioral skills that actually shape specific health behaviors (ie, injection of the HPV vaccine) [26] (see Fig. 1). The educational content of the mobile health intervention will cover the following topics: (1) basic health knowledge including information on the prevention of infectious diseases, vaccination, and sexual health, (2) information on HPV infection, cervix and cervical cancer, and the incidence and mortality rates of cervical cancer among Chinese women compared to the world average level, (3) introduction of the HPV vaccine as a preventive measure for cervical cancer, (4) case study showing the prognosis of Chinese women with advanced cervical cancer, (5) a story telling the experience of a female college student from being unaware of HPV to making a decision to vaccinate against HPV, (6) information on how to improve self-efficacy and self-determination in order to improve healthy behavior, and (7) behavioral techniques for HPV vaccination, including information on the availability and cost of the HPV vaccine at local clinics. The mobile health intervention will be delivered to each participant over 10 min each day for a 7-day period at each participant’s preferred time.

The mobile health intervention contains a high level of interactivity. Participants will be allowed to engage in mutual conversation amongst themselves on different topics of intervention. Based on the mobile application, the intervention group and the control group at each center will establish a chat group respectively, and the administrator will automatically upload 10 min of educational content in the intervention chat group only. After completing the learning session, participants can perform punching and talk about the educational content.

Control group(no intervention/ black control).

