## Methods/design

### Trial design

This is a multicenter, school-based, prospective, randomized, parallel group, double-blind, blank controlled trial involving a 7-day education intervention with a further 6 months follow-up. A total of 3360 individuals over 18 years old will be randomized to: (1) intervention group: this group will receive a baseline questionnaire followed by a 7-day mobile health education, and 3 questionnaire surveys at 1 month, 3 months, and 6 months after the intervention, or (2) control group: this group will receive 4 questionnaire surveys conducted simultaneously with the intervention group. This study protocol is reported in accordance with the Standard Protocol Items: Recommendations for Interventional Trials statement, and results will be reported in line with the Consolidated Standards of Reporting Trials (CONSORT) statement and the CONSORT statement for non-pharmacological interventions [27–29].

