#### Intervention procedure

Upon completion of the baseline assessment, two research staff will anonymize and number the students. The staff will then randomize participants to either the intervention group or control group. The intervention and control group will have at least 240 participants respectively at each of the seven centers. Timing randomization in this way ensures we can balance intervention and control groups on baseline characteristics. One unblinded research staff will remain in contact with participants via the mobile app. The intervention group will receive digital education materials every day during the 7-day intervention period, while the control group will not have any form of intervention. Possible intervention non-attendance and trial non-compliance will be collected and followed up via telephone by the unblinded researcher.

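### The blank control arm is given its own chat group, with no stated purpose or limit, leaving an avoidable route for HPV discussion among controls

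*Protocol article*

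**What the plan says.** The Interventions section of the protocol article introduces the social side of the programme with "The mobile health intervention contains a high level of interactivity" and explains it: "Participants will be allowed to engage in mutual conversation amongst themselves on different topics of intervention". It then sets up the channels: "the intervention group and the control group at each center will establish a chat group respectively". The lessons are confined to one of them: "the administrator will automatically upload 10 min of educational content in the intervention chat group only". After each lesson, "After completing the learning session, participants can perform punching and talk about the educational content".

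The comparator is described in three places, none of which mentions a chat group:

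- Trial design: "control group: this group will receive 4 questionnaire surveys conducted simultaneously with the intervention group".
- Interventions, at its end: "Control group(no intervention/ black control" (evidently a misprint for blank, the word used in the Trial design section).
- Intervention procedure: "while the control group will not have any form of intervention".

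**The concern.** Peer conversation is presented as a feature of the intervention, yet the channel that makes it possible is given to both arms. Only the educational upload is restricted to the intervention side; no restriction is placed on conversation. A reader therefore cannot tell whether the comparator is questionnaires alone or questionnaires plus a peer group on the study app.

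This matters beyond wording because the women in the control channel have been primed. They hear the research objectives at consent, then answer items on HPV knowledge, perceived barriers and benefits, susceptibility, subjective norms, intent and vaccination skills, with most of this repeated at 1, 3 and 6 months. A group formed around that experience could well talk about it, and a lesson forwarded by a classmate in the other arm could reach the whole control group of a centre in one post. Either would raise uptake, intent and knowledge among controls and shrink the estimated effect.

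**Working it through.** No figure in the plan is disputed. The check has three parts.

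**1. What each arm receives, by section**

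| Element | Intervention arm | Control arm | Section |
|---|---|---|---|
| Questionnaires | 4 | 4 | Trial design |
| Daily lesson, 7 days | yes | no | Interventions; Intervention procedure |
| Chat group on the app | yes | yes | Interventions |
| Talk about the lessons | yes | no lessons to discuss | Interventions |
| Contact and follow-up by app | yes | yes | Intervention procedure; 1-month follow-up |
| Stated rule on what may be posted | none | none | – |

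The education clearly differs between arms. The chat group is the one element that the control arm has but that the descriptions of the comparator leave out. Its purpose is not stated.

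**2. Who is in the control channel**

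The Sampling and randomization section gives 240 controls per centre, so 7 × 240 = 1680 in all. Phase 3 selects students by class. Phase 4 then randomises participants within each centre, stratified by major. Classmates can therefore fall into opposite arms, which gives lesson material a path into the control group.

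**3. What dilution would do (illustration only)**

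Inputs from the Sample size calculation section: 20% uptake in the intervention arm, 10% in the control arm, two-sided α = 0.05, 20% loss to follow-up. Evaluable numbers per arm: 240 × 0.8 = 192 per centre and 1680 × 0.8 = 1344 pooled. The raised control rates of 12% and 15% are assumptions with no source in the documents, and intervention uptake is held at 20%.

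- Difference = 0.20 − p_C
- OR = (0.20/0.80) ÷ (p_C/(1 − p_C))
- Power = Φ{[Δ√n − 1.96√(2p̄(1 − p̄))] ÷ √(0.20·0.80 + p_C(1 − p_C))}, where Δ is the difference, p̄ the mean of the two rates and n the number per arm; clustering is ignored

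| Control rate | Difference | OR | Power, one centre (192 per arm) | Power, pooled (1344 per arm) |
|---|---|---|---|---|
| 10% (plan) | 10 points | 0.25/0.1111 = 2.25 | 78.6% | >99% |
| 12% (assumed) | 8 points | 0.25/0.1364 = 1.83 | 57.1% | >99% |
| 15% (assumed) | 5 points | 0.25/0.1765 = 1.42 | 25.1% | 92.7% |

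For example, at 15% pooled: Δ√n = 0.05 × 36.66 = 1.833; p̄ = 0.175, so 1.96 × √0.28875 = 1.053; the denominator is √0.2875 = 0.536; (1.833 − 1.053)/0.536 = 1.45, and Φ = 0.927.

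Each point added to control uptake removes one point from the difference. The pooled comparison would still have ample power, so the harm would be a diluted effect measured against an unclear comparator, not a failed trial.

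**The case against.** A reader might infer that controls are in fact treated, because they have been given a component of the intervention. The documents do not support this. The lessons go to the intervention channel only, and the conversation described concerns the intervention's topics and follows a learning session that controls do not have. No section says that controls are given HPV topics to discuss. The app is also the route for contact and follow-up in both arms, and surveys are to be completed at about the same time, so a control chat group may be no more than a delivery channel. On that reading the descriptions of the comparator largely agree.

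Other points on that side also carry weight. Posting rules are operational detail that an article may leave to the full protocol. Women in the two arms can share classes, so some contamination is possible without any chat group. Parallel channels keep contact similar across arms, which has value in a trial described as double-blind, with participants unblinded only after 6 months and 7 days.

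These arguments rule out the stronger reading and any claim about size. They do not remove the point itself. The article does not merely omit a setting: it states that a control chat group will exist, in the paragraph that presents peer conversation as part of the intervention, while describing the comparator elsewhere as receiving nothing. Contamination through shared classes is a reason not to add a second route. The blinding argument is limited, since controls already see no lessons.

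**Conclusion.** The point holds in a limited form. The plan gives the control arm at each centre a chat group that its own descriptions of the comparator do not include, and nothing confines that group to contact and follow-up. It is an avoidable route for HPV discussion or reposted lessons among about 240 controls per centre. Any effect would dilute the estimate towards no difference and so would not produce a false positive. The documents give no basis for estimating its size: the 8-point and 5-point differences above follow entirely from assumed control rates. This is a cheap improvement to the design and its description, not a flaw that invalidates the comparison.

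**What to change.** In the Interventions section, state that the control channel is announcement-only: the administrator posts questionnaire links and reminders, worded identically in both arms, and members cannot post. Describe peer chat as a component of the intervention arm only. The Trial design, Interventions and Intervention procedure sections would then describe one comparator.

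If an open control chat is to be kept, remove the blank-control label and the statement in Intervention procedure that controls have no intervention of any kind. Describe the contrast as education with discussion versus a chat group without content, and limit the conclusions accordingly.

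The cost is one app setting and a sentence or two of text. The downsides are slightly less engagement in the control channel and a visible difference between the arms' channels. Follow-up rates should therefore be compared by arm, a small addition to the check of follow-up bias already planned in the Statistical analysis section.

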### Compliance

Attendance records will be used to assess the participants’ compliance with the intervention. This will occur the following day after each new educational content is uploaded. Furthermore, the number of participants in each questionnaire will be used to assess the participants’ compliance with the entire trial process.

### Procedure

To satisfy the study assessments, participants will complete a total of four electronic questionnaires (see Fig. 2). Electronic surveys will be carried out at approximately the same time (within 1 h) among the participants.

#### Screening

Potential participants will be identified for inclusion/exclusion criteria and those who are eligible will be provided with a written informed consent form. Individuals who agree to attend the study will be briefed on the function of the mobile app and core study measures.

#### Baseline

Prior to the intervention, the baseline survey will be conducted to assess socio-demographic and HPV vaccination status, sexual history, and knowledge, attitudes and beliefs about HPV and HPV vaccination.

#### Intervention procedure

Upon completion of the baseline assessment, two research staff will anonymize and number the students. The staff will then randomize participants to either the intervention group or control group. The intervention and control group will have at least 240 participants respectively at each of the seven centers. Timing randomization in this way ensures we can balance intervention and control groups on baseline characteristics. One unblinded research staff will remain in contact with participants via the mobile app. The intervention group will receive digital education materials every day during the 7-day intervention period, while the control group will not have any form of intervention. Possible intervention non-attendance and trial non-compliance will be collected and followed up via telephone by the unblinded researcher.

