#### 1-month follow-up

The participants in both the intervention and control groups will be followed up via the mobile app at 1 month after the intervention, and a questionnaire will be conducted simultaneously. Their HPV vaccination status and HPV related knowledge will be assessed. Likewise, their personal motivation, intention and relevant behavioral skills regarding the injection of the HPV vaccine will also be examined. In addition, the intervention group will assess their satisfaction with the intervention.

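### Telephone follow-up of trial non-compliance is given to the unblinded researcher, so the chasing of missed self-reported outcome questionnaires can differ by arm

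*Protocol article*

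**What the plan says.** All references are to the protocol article.

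- **Intervention procedure** gives one person two telephone tasks: "Possible intervention non-attendance and trial non-compliance will be collected and followed up via telephone by the unblinded researcher". It adds: "One unblinded research staff will remain in contact with participants via the mobile app".
- **Compliance** separates the same two ideas. For the intervention: "Attendance records will be used to assess the participants’ compliance with the intervention". For the trial: "the number of participants in each questionnaire will be used to assess the participants’ compliance with the entire trial process".
- **Blinding** states that "all researchers involved in outcome assessments will be blinded to the group allocation of participants", and describes unblinded contact for one period only: "During the intervention period, only unblinded researchers will be in contact with participants enrolled in the trial".
- **1-month follow-up** uses the same channel for both arms; participants "will be followed up via the mobile app at 1 month after the intervention, and a questionnaire will be conducted simultaneously". The 3-month and 6-month sections repeat the measures and mention no telephone calls.
- **Statistical analysis** says that participants complete the electronic forms themselves and that these upload automatically to a read-only database.

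**The concern.** Vaccination, appointment and intention are collected by self-completed questionnaire, and the article describes no check against vaccination records. No staff member rates the outcome. The main staff influence left is therefore who is prompted to respond, how persistently, and in what words. If that step belongs to someone who knows the allocation, effort can differ between arms without anyone intending it. Two things could follow: retention that differs by arm, and a personal prompt about the study that reaches one arm more than the other and may affect what is reported. The intervention arm is also the only one that can receive attendance calls, because educational content goes only to its chat group (Interventions). A later analysis could not readily separate either effect from the effect of the education.

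**Working it through.** The plan states no figure on this point, so there is none to reproduce. The check is a reading of the sections against each other, followed by an illustration of scale.

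**Reading the sections together**

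1. Compliance offers one measure of compliance with the trial process: participation in each questionnaire. The term trial non-compliance under Intervention procedure therefore most naturally means a missed questionnaire. This is an inference from the article's own measure; Intervention procedure does not spell it out.
2. Baseline is completed before randomization (Sampling and randomization, Phase 4; Intervention procedure). The other three questionnaires come 1, 3 and 6 months after the intervention (Measures). None falls within the 7 days.
3. So, on that reading, calls about missed questionnaires after allocation can concern only the 1-, 3- and 6-month questionnaires, which carry the outcomes.
4. Blinding places unblinded contact in the intervention period and does not say who contacts participants afterwards. Intervention procedure, read this way, carries the unblinded role into outcome collection.

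**Illustration of scale**

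Inputs from Sample size calculation: 10% uptake in controls, a planned difference of 10 points (20% against 10%), 20% loss, and 240 per group in 7 centers, which is 1,680 per arm. Assumption: no true effect, so p = 0.10 in both arms.

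*Pattern A (assumed): chasing recovers vaccinated intervention students more readily.* Let r1 and r0 be the response rates of vaccinated and unvaccinated students.

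Observed rate = p·r1 / (p·r1 + (1 − p)·r0)

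Controls, r1 = r0 = 0.80: 0.08/0.80 = 10.0%. Intervention arm, r0 = 0.80:

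| r1 | Observed rate | Spurious difference | Difference if non-responders count as unvaccinated |
|---|---|---|---|
| 0.85 | 0.085/0.805 = 10.56% | 0.6 points | 8.5% − 8.0% = 0.5 |
| 0.90 | 0.090/0.810 = 11.11% | 1.1 points | 9.0% − 8.0% = 1.0 |
| 0.95 | 0.095/0.815 = 11.66% | 1.7 points | 9.5% − 8.0% = 1.5 |
| 1.00 | 0.100/0.820 = 12.20% | 2.2 points | 10.0% − 8.0% = 2.0 |

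*Pattern B (assumed): every lost student is unvaccinated, and the intervention arm is retained better.*

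- Losses of 17.5% (intervention) and 22.5% (control): 0.10/0.825 − 0.10/0.775 = 12.12% − 12.90% = −0.8 points.
- Losses of 15% and 25%: 0.10/0.85 − 0.10/0.75 = 11.76% − 13.33% = −1.6 points.
- Counting non-responders as unvaccinated gives 10% in both arms and no bias.

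*Against sampling error.* With 1,680 × 0.80 = 1,344 respondents per arm and independent responses, SE = √(2 × 0.10 × 0.90/1,344) = 1.16 points. Pattern A therefore spans about 0.5 to 1.9 standard errors (0.56/1.16 to 2.20/1.16).

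**The case against.** The strongest reply is that nothing in the article is breached. The blinding statement covers researchers who assess outcomes. Here the participant fills in the form, the form uploads itself, and surveys run at about the same time for everyone. Reminding a student to open a form is retention work. A reader might infer a direct contradiction between Intervention procedure and Blinding, but the text does not support that, because nothing says the caller takes, records or rates an answer. This part of the reply stands.

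The second reply concerns timing: the sentence sits under Intervention procedure, right after the 7-day delivery, and does not say that the role continues to 1, 3 and 6 months. It is true that the time span is unstated. But no questionnaire falls in those 7 days, so limiting the sentence to them would leave questionnaire non-compliance with nothing to refer to.

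Third, a reader might suppose that intervention students generally come to know the caller by telephone. That is not supported: only possible non-attenders are called, their number is not given, and both arms have a chat group.

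Fourth, the figures rest on assumptions, and harder chasing of the intervention arm could even lower its observed uptake (Pattern B). The article specifies intention-to-treat, and the handling of missing data may be set out in a document not shown. This also stands. It limits what can be said about size, but counting non-responders as unvaccinated removes the bias only in Pattern B, not in Pattern A.

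Finally, having blinded outcome staff make the calls would invite students to reveal their arm. That is a fair warning about the remedy, and the fix below takes account of it.

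**Conclusion.** The point holds as a modest weakness in a stated procedure. On the best-supported reading, an arm-aware person chases missing self-reported outcome questionnaires. This undermines the purpose of blinded outcome assessment without contradicting its wording.

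The size and direction of any bias are unknown. With no true effect, 10% uptake and 80% response as the starting point, selective recovery of vaccinated intervention students gives about 0.6 to 2.2 percentage points, while better retention of unvaccinated ones gives a bias of the opposite sign. Either is small beside the planned 10 points, though not negligible beside a standard error of about 1.2.

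A reader might go further and quote an inflated false-positive rate: with that standard error, an assumed artefact of 1 point gives about 14%, and of 2 points about 41%. The arithmetic is right, but it only converts an assumed bias into an error rate. The documents give no basis for expecting a bias of that size or direction, so these rates should not be presented as the expected consequence. The case for change is that it is cheap and removes a source of bias that would be hard to correct afterwards.

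**What to change.** 1. In Intervention procedure, limit the unblinded researcher's telephone follow-up to attendance during the 7-day intervention.
2. Prompt missed 1-, 3- and 6-month questionnaires by automated app reminders with the same wording, number and timing in both arms and no HPV content.
3. If calls prove necessary, use one neutral script in both arms, delivered by staff who neither assess outcomes nor analyse data and who are not told the allocation. A student who reveals her arm then unblinds nobody whose blinding matters to the results.
4. Report questionnaire response by arm at each time point.

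This takes a few lines of text and brings Blinding, Compliance and Intervention procedure into line. The cost is setting up the reminders and possibly losing some of the retention that a personal call would secure. It does not remove the participants' own knowledge of whether they received the education, which remains whoever sends the reminder.
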